**Methods:**

A pre–post-implementation study will be conducted in three hospitals: two non-metropolitan sites in the Mid-North Coast Local Health District (MNCLHD) and one metropolitan site in the Nepean Blue Mountains Local Health District (NBMLHD). An education program will be delivered to clinicians with written resources and clinical support. All children and young people aged 0–18 years with T1D receiving care at these sites receive SWIIM for diabetes management. Data will be collected over an 18-month implementation period with retrospective pre-intervention data for comparison. The primary outcome was the change in HbA1c levels over the implementation period. Secondary outcomes included continuous glucose monitoring (CGM) metrics, insulin therapy modality, adherence to complication screening, hospitalization rates, and program feasibility indicators. Acceptability will be assessed using validated patient- and clinician-reported measures. A cost-effectiveness analysis will be performed to determine the financial impact of implementing the SWIIM over standard care.

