
The model of care will be delivered to families with the following components:

Inpatient insulin initiation and education program for newly diagnosed type 1 diabetes: A standardized education package for newly diagnosed type 1 diabetes was delivered by diabetes nurse educators, dietitians, and social workers over a 5–7-day inpatient admission. Medical officers initiate and adjust subcutaneous insulin doses. Receipt of education is verified by an education checklist completed by families and educators and a carbohydrate counting quiz performed prior to discharge. Following discharge, daily phone follow-ups for ongoing education and insulin dose adjustment were provided for 7–10 days.Three monthly outpatient follow-ups: Young people will be reviewed by a diabetes educator and dietitian 2 weeks after diagnosis. Thereafter, young people are reviewed in outpatient clinics four times per year by physicians. At least one review each with the diabetes educator, dietitian, and social worker (where available) is arranged annually. During outpatient appointments, insulin doses are titrated, and SWIIM management principles are communicated to patients and families.School education: Schools, preschools, and daycare centers that each patient attended received educational session delivered by a diabetes educator. An individualized school plan was provided for each patient. Schools can contact diabetes educators by phone during business hours. The school visit is repeated if there is a change in therapy or the child attends a new school.Written resources: A printed 10 Essential Habits document summarizing key SWIIM principles will be provided to all families from the initial inpatient admission or at the first outpatient clinic review during implementation. Additional printed resources will be provided to the local teams and distributed by clinicians at their discretion, including written and pictorial dietary guidance, insulin dosing guidance, and exercise management strategies. Pro forma for individualized written plans for schools, day care centers, and camps will be provided to local teams.Insulin pump therapy initiation: Patients and families who wish to commence insulin pump therapy will be enrolled in an outpatient education program comprising a 1-hour group pre-pump education workshop with a diabetes educator and dietitian, followed by a 1-hour face-to-face session with the educator and pump company representative for commencement of the pump. Daily phone follow-up was provided for the week after pump initiation to adjust insulin doses until euglycemia was achieved. Insulin pump therapy is not commenced until at least 3–6 months after diagnosis to allow for maximal familiarization with MDI administration.Stabilization admissions: At the team’s discretion, elective admissions to the hospital are utilized to repeat the inpatient education program and adjust insulin doses.Hospital staff education: A hospital procedure document on insulin administration, hypoglycemia management, mealtime routine, and glycemic target is available in hard copy on pediatric wards and on the hospital intranet. Thirty-minute face-to-face training sessions with ward nursing staff are delivered by diabetes educators or dietitians at 3–4 monthly intervals, or as requested by ward staff. Dietitians oversee carbohydrate counting of hospital meals to allow for accurate insulin dosing in hospitals. A written dietary guide, individualized to the child’s age, was provided to the nursing staff to inform them of the appropriate carbohydrate quantities for each meal and snack.

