
### Implementation intervention

A multi-component clinical practice change intervention will be implemented at each site over an 18-month phase to support embedding SWIIM into the participating sites. Clinicians will be supported to provide the SWIIM program as part of the routine inpatient and outpatient management of T1D in children and adolescents. Through collaborative review with JHCH and implementation site clinicians, aspects of both inpatient and outpatient delivery of SWIIM may be adjusted to suit the local context and the available resources. Deviations from the standard SWIIM implementation will be reported in the final analysis.

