#### Secondary clinical outcome measures

Additional patient clinical outcome data were obtained from the electronic medical records at the MNCLHD and NBMLHD sites throughout the pre-intervention and implementation periods. The collected data included:

Body mass index (BMI) and BMI standard deviation.Method of insulin administration (fixed insulin dose regimes, flexible multiple daily injections, insulin pump therapy).CGM metrics: Sensor wear time, time in range (3.9 mmol/L–10.0 mmol/L, 70 mg/dL–180 mg/dL), time in tight range (3.9 mmol/L–7.8 mmol/L), time below range (<3.9 mmol/L, <70 mg/dL), time in hypoglycemia, level 2 (<3.0 mmol/L, <54 mg/dL), time above range (>10 mmol/L, >180 mg/dL), and time in hyperglycemia, level 2 (>13.9 mmol/L, >250 mg/dL).Adherence to international recommendations for diabetes-related complication screening (30) in the 12 months preceding implementation to study completion.Number of hospitalizations for diabetes in the 12 months preceding implementation to study completion (not including initial diagnosis).

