#### Cost effectiveness analysis

The value for money of SWIIM will be addressed in a cost-effectiveness analysis (CEA) of the study cohort to determine whether SWIIM is more cost-effective than usual care in reducing the clinical average HbA1c for young people living with type 1 diabetes, where usual care and intervention periods are defined by pre-post comparison at each site. Economic results will be reported as incremental cost-effectiveness ratios. A sensitivity analysis will be conducted to explore the robustness of the results to uncertainties around key parameters.

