### Power and sample size calculation

Based on the analysis of longitudinal JHCH clinical data, the within-patient variability for HbA1c is low (standard deviation of 0.6% over a 12-month period). To detect a change in HbA1c of 1% at a significance level of 0.05 with power 0.9, the sample size across the three sites needed is 25. If the within-patient variability at the three sites was double that of JHCH (standard deviation of 1.2%), the required sample size would be 90. Allowing for a loss-to-follow-up of 10%, we would aim to recruit a minimum of 100 patients at baseline. There are currently 330 patients across the three sites, and recruitment will continue throughout the study for newly diagnosed patients, with a potential sample size of approximately 400 at study close. This would allow for a recruitment rate of 33% to ensure that the sample size is met.

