### Statistical analysis

The primary analysis will evaluate the change in glycemic control, measured by HbA1c at the individual level, from the 6-month pre-implementation baseline period to the end of the 18-month implementation period. Data will be modeled at the patient level, with clinic means over time used as the primary summary measure for interpretation.

A linear mixed-effects segmented regression model will be fitted, with fixed effects for time pre-intervention (monthly index), period (0 = per-implementation, 1 = implementation), time post intervention (which is zero during pre-intervention months and increments monthly thereafter), site, and patient-level covariates: age, sex, diabetes duration, Aboriginal and Torres Strait Islander status, and SEIFA quintile. The model will include a random intercept for patients to account for potential repeated measurements, and an autoregressive (AR(1)) correlation structure will be examined to account for within-patient autocorrelation over time. Effects will be expressed as (i) immediate level change and (ii) change in monthly slope, both relative to the counterfactual pre-implementation trends. Robust (sandwich) standard errors were calculated. Distributional and other modelling assumptions will be assessed by inspecting residual plots, with transformations or different distributional families (e.g., proportional odds logistic models) considered. Secondary outcomes with repeated measures will be assessed using a similar model with an appropriate distributional family dependent on the outcome type.

To assess the impact of medical outreach clinics in the MNCLHD prior to the study onset, an additional comparison of the primary outcome will be made from the commencement of medical outreach clinics to the commencement of the implementation period.

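### The hospitalization outcome counts the elective stabilization admissions that SWIIM itself prescribes, so a change in the total cannot by itself be read as clinical benefit or harm

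*Protocol article*

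**What the plan says.** The protocol article, under Secondary clinical outcome measures, lists "Number of hospitalizations for diabetes in the 12 months preceding implementation to study completion (not including initial diagnosis"). That parenthesis holds the only exclusion. The abstract's Methods confirm the secondary role: "Secondary outcomes included continuous glucose monitoring (CGM) metrics, insulin therapy modality, adherence to complication screening, hospitalization rates, and program feasibility indicators".

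The section on the SWIIM model of care introduces its list with "The model of care will be delivered to families with the following components". One listed component is the stabilization admission. When the team sees fit, "elective admissions to the hospital are utilized to repeat the inpatient education program and adjust insulin doses".

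Under Implementation intervention, sites have latitude: "aspects of both inpatient and outpatient delivery of SWIIM may be adjusted to suit the local context and the available resources". Departures from standard SWIIM are to be reported in the final analysis.

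For the analysis, the Statistical analysis section says only that "Secondary outcomes with repeated measures will be assessed using a similar model with an appropriate distributional family dependent on the outcome type". The article nowhere separates elective from unplanned admissions, and it does not say whether the sites used elective stabilization stays before implementation.

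**The concern.** A stabilization stay is a hospital admission for diabetes that is not the admission at diagnosis, so the stated rule includes it. The rule removes one planned SWIIM admission, the initial education stay, and keeps the other. The intervention can therefore generate events in an outcome listed as clinical.

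Two misreadings follow. A real fall in unplanned admissions (ketoacidosis, severe hypoglycaemia, other acute causes) could be masked or reversed by added elective stays. A rise in the total could be taken for harm when it is only the programme being delivered. Because sites may adapt inpatient delivery, the mixture may also differ between them. There is no concurrent control group, so the before-after change carries the whole inference. A suitable distributional family cannot separate admission types that were never classified.

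**Working it through.** The documents state no rate, effect size or power for hospitalizations, so there is no figure of the plan's own to reproduce. The first step is a reading of the text. The rest is illustration.

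**Reading.** The outcome is diabetes admissions minus the admission at diagnosis. SWIIM adds discretionary elective diabetes admissions after diagnosis. The second set lies inside the first.

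**Inputs from the documents.** A 12-month look-back and an 18-month implementation period; a recruitment minimum ("we would aim to recruit a minimum of 100 patients at baseline"); 330 current patients across the sites.

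**Assumed inputs.** Unplanned rate before, *u* = 10 per 100 patient-years (range 5 to 20). True fall in unplanned admissions 30% (range 20% to 40%), so the true rate ratio is *R* = 0.70.

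**Elective rate that cancels the benefit.** Let *e0* and *e1* be the elective rates before and after. The ratio computed from the total is (*uR* + *e1*) / (*u* + *e0*). It equals 1 when *e1* − *e0* = *u*(1 − *R*).
- Central case: 10 × 0.30 = 3 per 100 patient-years.
- Range: 5 × 0.20 = 1 to 20 × 0.40 = 8.

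**In admissions, central case.**
- 100 patients × 1.5 years = 150 patient-years; 0.03 × 150 = 4.5 stays.
- 330 patients × 1.5 years = 495 patient-years; 0.03 × 495 = 14.85 stays.
- Per patient: 0.03 × 1.5 = 0.045, about 1 in 22.

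**Ratio from the total when the true ratio is 0.70, *u* = 10 and *e0* = 0.**

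| Elective stays per 100 patient-years after | Ratio from the total |
|---|---|
| 1 | (7 + 1)/10 = 0.80 |
| 3 | (7 + 3)/10 = 1.00 |
| 6 | (7 + 6)/10 = 1.30 |

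**Same total, different truths.** Assume 20 unplanned admissions before, equal follow-up and no elective stays before. A ratio of 1.00 then arises from no true change with 0 elective stays (20/20), a true 25% fall with 5 (15 + 5 = 20), or a true 50% fall with 10 (10 + 10 = 20). The total cannot tell these apart.

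**If elective use does not change.** With *e0* = *e1* = 3 and *u* = 10, the ratio is (7 + 3)/(10 + 3) = 0.77. The effect is diluted but keeps its direction.

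**Precision of the unplanned count alone** (*u* = 10, *R* = 0.70; every patient contributes to both full windows; independent Poisson counts).
- 330 patients: 33.0 events before (330 patient-years) and 0.07 × 495 = 34.65 after. exp(1.96 × √(1/33.0 + 1/34.65)) = 1.61, so the 95% interval is 0.70/1.61 to 0.70 × 1.61, or 0.43 to 1.13.
- 100 patients: 10.0 and 10.5 events. The factor is 2.38 and the interval 0.29 to 1.66.

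**The case against.** The strongest reply is that the outcome is a one-line item in a condensed article. Coding by planned status or cause may sit in a data dictionary, full protocol or analysis plan that is not shown, and one stated exclusion need not be the complete list. This does not dispose of the point. The article does not leave the exclusion open. It states one, and that exclusion removes one planned SWIIM stay and keeps the other. Followed exactly, the rule gives the mixed total.

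A second reply is that the plan never says a change in admissions will be read as benefit or harm, and that it advises caution about causal attribution. That is true, but the item is headed as a clinical outcome, and general caution does not tell a reader which part of the total moved. Reporting departures from standard SWIIM helps only partly, since stabilization stays are part of the standard model.

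A third reply is that the distortion needs a net increase in elective stays. Outreach clinics from the originating hospital began at the Mid-North Coast sites 24 months before the study, so some elective use beforehand is possible. This stands: the distortion could be small, and every rate above is assumed. Without classification, however, nobody could find out.

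It is also fair that all diabetes admissions are a legitimate measure of burden and resource use. The total should be kept for that purpose.

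**Conclusion.** The point holds, at minor severity. The outcome as defined includes admissions that SWIIM itself prescribes, so a change in the total is not interpretable on its own as clinical benefit or harm. The direction of bias against SWIIM depends on elective stays increasing after implementation. That is plausible because they belong to the model being introduced, but it is not documented.

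The size is unknown. Under the assumed rates, a net increase of 3 elective stays per 100 patient-years (range 1 to 8) would erase a true fall in unplanned admissions, and 6 would turn a true ratio of 0.70 into 1.30.

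The HbA1c primary analysis and the sample size are not touched. CGM time below 3.0 mmol/L is already collected as a separate hypoglycaemia signal.

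**What to change.** In the planned extraction from the electronic medical record, classify each diabetes admission as elective stabilization or unplanned, and record the cause of each unplanned one (ketoacidosis, severe hypoglycaemia, other). Then:

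- Use unplanned diabetes admissions per patient-year, in the 12 months before and the 18 months of implementation, as the clinical outcome. Keep cause-specific rates descriptive.
- Report elective stabilization admissions separately, by site and period, as intervention delivery and resource use.
- Keep total admissions for the cost-effectiveness analysis, where "usual care and intervention periods are defined by pre-post comparison at each site" and every stay has a cost.

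The cost is one extra field in work already planned. There are two drawbacks. Unplanned counts will be small: the illustrative intervals of 0.43 to 1.13 (330 patients) and 0.29 to 1.66 (100 patients) both include 1, and repeat admissions in the same patients would widen them. The split corrects what the outcome means, not how precisely it is estimated. Retrospective coding of planned against unplanned status may also be imperfect, so unclassifiable admissions should be reported as such.

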#### Feasibility of program implementation

Feasibility will be assessed by patient-reported receipt of diabetes-related education as part of the SWIIM program using a diabetes education checklist. The written diabetes education checklist is completed during all inpatient admissions for new diagnoses of T1D by the diabetes educator, dietitian, and family to acknowledge receipt of diabetes-related education. Adherence to follow-up will be assessed by the number of outpatient episodes with the physician, diabetes educator, and dietitian per year. The Australian type 1 diabetes guideline recommendations will be used as targets (three to four outpatient reviews per year and at least one comprehensive review per year with a diabetes educator and dietitian) (31). Checklist completion data and outpatient clinic attendance will be collected from electronic medical records.

#### End-user acceptability of care

At the initial outpatient visit, clinic staff will administer the Diabetes Treatment Satisfaction Questionnaire (DTSQ) and Problem Area in Diabetes (PAID) Scale to patients with a duration of diabetes of at least 12 months. Participants will have the opportunity to complete this on a digital tablet, paper form, or their own digital device. The DTSQ is a validated survey for rating satisfaction with diabetes treatment and can be repeated to assess changes in satisfaction over time following a new intervention (32). Parent and adolescent versions will be administered as part of the study. The PAID is a widely used measure of diabetes-related distress with demonstrated validity and reliability for the 8–12 (child) and 12–18 year (teen) age ranges (33, 34). Questionnaires will be completed by accompanying carers and children and young people aged 8 years and over at six monthly time points to assess changes in treatment satisfaction and diabetes-related distress following the implementation of SWIIM.

#### Clinician acceptability of care

An electronic multiple-choice questionnaire and semi-structured interview will be conducted at two time points (commencement of implementation and study completion) with the diabetes team clinicians. A SWIIM program-specific 9-item questionnaire was developed by the research staff to rate satisfaction and confidence with diabetes management, team cohesion, and identify barriers and enablers to SWIIM implementation. Changes in the rated satisfaction from the questionnaire will be reported. Thematic analysis will be conducted on the interviews to develop a conceptual model of the key enablers and barriers to SWIIM implementation.

#### Cost effectiveness analysis

The value for money of SWIIM will be addressed in a cost-effectiveness analysis (CEA) of the study cohort to determine whether SWIIM is more cost-effective than usual care in reducing the clinical average HbA1c for young people living with type 1 diabetes, where usual care and intervention periods are defined by pre-post comparison at each site. Economic results will be reported as incremental cost-effectiveness ratios. A sensitivity analysis will be conducted to explore the robustness of the results to uncertainties around key parameters.

### Data collection and storage

All data will be stored in a REDCap database administered by the Hunter Medical Research Institute and retained for 15 years. Any potentially identifiable information obtained for this research project will be treated as confidential and securely stored. Information will be coded and de-identified as necessary. Data will be available only to primary researchers and statisticians.

### Power and sample size calculation

Based on the analysis of longitudinal JHCH clinical data, the within-patient variability for HbA1c is low (standard deviation of 0.6% over a 12-month period). To detect a change in HbA1c of 1% at a significance level of 0.05 with power 0.9, the sample size across the three sites needed is 25. If the within-patient variability at the three sites was double that of JHCH (standard deviation of 1.2%), the required sample size would be 90. Allowing for a loss-to-follow-up of 10%, we would aim to recruit a minimum of 100 patients at baseline. There are currently 330 patients across the three sites, and recruitment will continue throughout the study for newly diagnosed patients, with a potential sample size of approximately 400 at study close. This would allow for a recruitment rate of 33% to ensure that the sample size is met.

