## Methods

### Study design and setting

A pre-post implementation study will be conducted at three sites providing outpatient and inpatient pediatric diabetes care in New South Wales (NSW), Australia. Two of the sites (Port Macquarie and Coffs Harbour) are level 5 public hospitals in the Mid-North Coast Local Health District (MNCLHD). The third center (Nepean) was a level 6 tertiary public hospital in the metropolitan Nepean Blue Mountains Local Health District (NBMLHD). The characteristics of the health districts in comparison to the JHCH, where SWIIM was developed, are presented in **Supplementary Table 2**. The sites were selected to allow analysis of SWIIM implementation in a variety of settings with differing staffing levels and diabetes-specific expertise across metropolitan and non-metropolitan populations.

The implementation of a practice change intervention will occur over an 18-month period (**Supplementary F****igure 1**), during which eligible patients will be recruited. The intervention will be delivered simultaneously across the three sites. Given that the intervention occurs at a site-wide level, a within-center randomization protocol would not be possible. Pre-intervention (usual care) data will be retrospectively obtained from the electronic medical records of recruited the patients. Patients who are newly diagnosed during the study period or for whom retrospective data are not available will also be included for statistical analysis at the available time points (see *Statistical analysis*).

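### The required sample sizes of 25 and 90 do not follow from the stated inputs (1% change, SD 0.6% or 1.2%, significance level 0.05, power 0.9) under any simple pre-post test

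*Protocol article*

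**What the plan says.** All inputs are in the protocol article, under Power and sample size calculation.

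- Variability: "the within-patient variability for HbA1c is low (standard deviation of 0.6% over a 12-month period", from longitudinal data at the developing hospital.
- Target, level and power: "To detect a change in HbA1c of 1% at a significance level of 0.05 with power 0.9".
- First result: "at a significance level of 0.05 with power 0.9, the sample size across the three sites needed is 25".
- Second result, with the SD doubled: "double that of JHCH (standard deviation of 1.2%), the required sample size would be 90".
- Recruitment target: "Allowing for a loss-to-follow-up of 10%, we would aim to recruit a minimum of 100 patients at baseline".

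The section does not name the test, its sidedness, the SD of the change, or any inflation factor other than loss to follow-up. The Statistical analysis section gives no other significance level, so 0.05 is the only one in the document. The design compares periods within the same patients where records allow. Under Study design and setting: "Pre-intervention (usual care) data will be retrospectively obtained from the electronic medical records" of the recruited patients.

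**The concern.** The article prints a complete set of inputs for a standard calculation (effect, SD, significance level, power) and two results. A reader who puts the inputs into any usual pre-post formula gets clearly smaller numbers. Either an input is misreported or the results are. The minimum of 100 patients, and the recruitment rate of 33% that is meant to secure it, both rest on the figure of 90. As printed, the justification of the sample size cannot be verified.

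**Working it through.** **Inputs** (Power and sample size calculation): change Δ = 1; SD s = 0.6 or 1.2; significance level 0.05; power 0.90. Sidedness is not given, so both were tried.

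**Formulas** (exact, noncentral t):

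- Paired: noncentrality = √n × Δ / SD of change, with n − 1 degrees of freedom. The SD of change is taken first as s, then as s × √2 (s read as the SD of a single value, with independent values).
- Two-sample: noncentrality = Δ / (s × √(1/n₁ + 1/n₂)), with n₁ + n₂ − 2 degrees of freedom.

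The required size is the smallest n with power of at least 0.90.

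**Attempt to reproduce 25 and 90 at 0.05:**

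| Test | Two-sided 0.05, SD 0.6 / 1.2 | One-sided 0.05, SD 0.6 / 1.2 |
|---|---|---|
| Paired, SD of change = s | 7 / 18 | 5 / 14 |
| Paired, SD of change = s × √2 | 10 / 33 | 8 / 27 |
| Two-sample, total, equal groups | 18 / 64 | 14 / 52 |
| Protocol article | 25 / 90 | 25 / 90 |

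If half-patient groups are allowed, the 64 becomes 63. The normal approximation gives smaller numbers again: 4 / 16, 8 / 31 and 16 / 62 at two-sided 0.05. The nearest results, from the two-sample test, are 28% and 29% below the printed ones (1 − 18/25 = 0.28; 1 − 64/90 = 0.29), so rounding does not explain the gap.

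**Power of the printed sizes at two-sided 0.05:**

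- Two-sample, 25 in total (12 and 13), SD 0.6: 0.979.
- Two-sample, 90 in total, SD 1.2: 0.974.
- Either paired version: above 0.999 in both cases.

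**Loss to follow-up:** 90 / (1 − 0.10) = 100. This step is correct and comes after the figure of 90, so it cannot explain the gap.

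**What would give 25 and 90?** Several departures from the printed inputs do:

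| Assumption | SD 0.6 | SD 1.2 |
|---|---|---|
| Two-sample, two-sided 0.01, power 0.90 | 25 (26 with equal groups) | 90 |
| Two-sample, two-sided 0.025, power 0.95 | 25 (26 with equal groups) | 90 |
| Two-sample, two-sided 0.05, power 0.90, inflated by 1.4 | 18 × 1.4 = 25.2 | 64 × 1.4 = 89.6 |

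Powering each site separately fits less well. With the normal approximation and SD of change s × √2, the n per site is (1.960 + 1.282)² × 2s² = 7.57 and 30.26. Three times that is 22.7 and 90.8, or 24 and 93 when each site is rounded up. It also conflicts with the statement that 25 is the number over all sites.

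**The case against.** **The discrepancy is harmless.** On every 0.05 calculation above, the printed sizes exceed the need, and 330 patients are already under care at the sites, with about 400 expected by study close. This stands, and it limits the weight of the point. It does not make the printed figures correct.

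**A condensed article may leave out the test, the sidedness or an inflation factor.** True, and their absence alone would be no finding. Here, however, the article prints both inputs and results, and the two do not agree as printed.

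**A reader might infer that the study was really sized at two-sided 0.01, and that the primary test therefore has two competing thresholds.** The match at 0.01 is close: 25 patients (12 and 13) give power 0.8999, and 90 give 0.9036. The documents still do not support the inference, for three reasons:

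- Two printed numbers cannot separate significance level, power and inflation. Two-sided 0.025 with power 0.95 fits equally well, as does a factor of 1.4.
- The 0.01 match needs the within-patient SD to be entered in an independent-groups formula (or an SD of change of 2 × s). A paired test at 0.01 gives 9 / 25, or 15 / 47 with s × √2.
- The article nowhere mentions 0.01. Its only level is 0.05, so there is no second threshold under which a p-value between 0.01 and 0.05 would be read differently, and no basis for moving the primary test to 0.01.

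**Replacing 25 and 90 with 18 and 64 would only print exact-looking numbers for a test that is not planned.** This is fair. The primary analysis is a patient-level mixed-effects segmented regression. The remedy is a calculation whose method is named, not the adoption of the two-sample figures as such.

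**Conclusion.** The point holds as an arithmetic inconsistency. The sizes of 25 and 90 are not delivered by a 1% change, SD 0.6% or 1.2%, significance level 0.05 and power 0.9 under a paired or an equal-group two-sample t-test, whether one- or two-sided. Against the closest version (two-sample, two-sided 0.05), the printed sizes are about 1.4 times the requirement (25/18 = 1.39; 90/64 = 1.41). Equivalently, the power is about 98% and 97% instead of 90%.

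The error is in the conservative direction, so on this point the study is not underpowered for a simple 1% mean change. That statement covers these simple tests only, not the level and slope terms of the segmented model. The source of the discrepancy cannot be determined from the article. The conclusion assumes that the inputs are meant as printed and that no unstated adjustment was applied.

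**What to change.** Revise the paragraph under Power and sample size calculation:

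1. Keep 0.05 as the significance level of the primary test and state its sidedness.
2. Name the test used for sizing, the SD of change and how it was obtained from 0.6% and 1.2%, and any inflation factor.
3. Restate the required sizes, or the power achieved with 25 and 90, so that they follow from those inputs. For illustration, a two-sample test at two-sided 0.05 needs 18 and 64, and 64 / 0.9 = 71.1 gives 72 after loss to follow-up. A paired test with s × √2 needs 10 and 33, and 33 / 0.9 = 36.7 gives 37.
4. If another significance level, power or inflation was used for sizing, report it as a sizing assumption, separate from the level of the primary test.
5. Present 100 as a chosen recruitment target above the requirement.

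The cost is rewording one paragraph. No extra patients or data are needed, and recruitment does not change.
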